**Methods/Design:**

A two-arm randomized controlled trial design will be adopted. Eligible working adults will be randomly allocated to either the intervention group or the waiting-list control group, with 177 participants in each arm. The intervention, which consists of four web-based training sessions, each targeting one of the psychological capital components (hope, efficacy, optimism and resilience), will be implemented over a 4-week period. On-line surveys will assess the participants in each group at baseline, intervention completion, 1 and 3 months after the completion. The primary outcome is individuals’ psychological capital level; secondary outcomes include individuals’ well-being, depressive symptoms, work engagement and productivity. Return-on-investment will be calculated from the employers’ perspective based on productivity gain, savings in medical expenditure, as well as operation and time costs. Analysis will follow the intention-to-treat principle.

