### Sample size

Based on the existing evidence from PPIs, we expect to find a standard effect size of 0.3 or larger comparing the intervention group with the control group [14]. To achieve a statistical power of 80%, given a two-sided alpha of 0.05, we need at least 177 participants in each condition, i.e. a sample size of 354 or more.

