### Outcome assessment

The primary outcome is the level of psychological capital. The secondary outcomes include well-being, depressive symptoms, work engagement and economic cost-benefit (as measured by work productivity, medical expenditure and time cost for using the website). All these measures are self-reported, and will be collected through the *Happy@Work* website. Assessments will be made at the baseline, immediately after individuals finish the 4-week trainings, and at 1 and 3 months follow-up after the completion. All the measurements, except specified, will be assessed in both control and intervention groups.

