### Work engagement and ROI related measures

The Utrecht Work Engagement Scale - shorten version (UWES) [51] will be used to measure engagement. It is a 9-item self-rating scale with item scores from 0 to 6. It has an excellent internal consistency (e.g. Cronbach’s alpha varied between 0.85 to 0.92 across different samples from 10 countries [52]).

Work productivity changes will be measured by the WHO’s Health and Performance at Work Questionnaire - short form (HPQ) [53], which obtains information on individuals’ past 4 weeks productivity through assessing both absenteeism and presenteeism. It is currently unavailable in traditional Chinese. A standard ’translation and back-translation’ process was adopted to translate it into traditional Chinese [54]. We pre-tested the Chinese version before making further improvement.

The other two components for calculating the ROI besides work productivity are medical costs and time costs. To obtain these two measures, participants in both control and intervention groups will be asked to report the past-month medical expenditures and the share paid by their employers (if any); while the intervention group alone will also report time they spend on the entire trainings.

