### Data analysis

Results will be reported according to the Consolidated Standards of Reporting Trials (CONSORT) statement regarding eHealth [55]. The primary data analysis will follow the intention-to-treat principle and compare the differences in the above outcome measures between the intervention group and the wait-list control group. Because of the potential dropout, missing data is expected. When appropriate, we will use the expectation-maximization (EM) method to impute missing data [56]. In addition, per-protocol analysis will also be conducted.

The two groups will first be described in terms of their baseline characteristics. The primary data analysis will compare the effectiveness of *Happy@Work* in the intervention group with the changes in the control group, based on the differences on PsyCap-24, WEMWS, SWLS, CES-D and UWES. Repeated measures of ANOVA will be used to check the multivariate main effects of intervention (compared with control) and time (pre, post, follow-up), as well as their interaction effect. A two-sided P value of 0.05 or less will be considered as significant. We will compute the standardized effect size (Cohen’s d) as well. Moderator analysis will also be conducted to explore which sub-group/s would benefit more from the intervention, by regressing outcome variables on independent variables like age, gender, education and baseline CES-D scores. Work productivity change will be compared between these two groups as well. SPSS V.18 will be used for the data analysis.

To make the business case for similar type of interventions, return-on-investment of the program will be calculated from the employers’ perspective using the following formula:

ROI = (Gain from investment - Cost of investment)/Cost of the investment;

where, *Gain from investment* = total monetized value of employees’ work productivity gains + savings in employers’ share of medical cost; and

*Cost of investment* = Program designing and operation costs (assuming employers self-fund similar programs) + the monetized time cost (if employees use work time for the program training*).*

Self-reported monthly salary will be used to monetize the work productivity changes and time cost for each individual. All the afore-mentioned items will be the incremental value compared with the control group.

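### Work productivity and the ROI gain are described as before-after changes with no baseline adjustment named; the contrast is unbiased, but adjusting for baseline would make it more precise at almost no cost

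*Protocol article*

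**What the plan says.** Under Work engagement and ROI related measures, productivity is taken from the HPQ short form, which "obtains information on individuals’ past 4 weeks productivity through assessing both absenteeism and presenteeism". The Outcome assessment section sets the timing: "Assessments will be made at the baseline, immediately after individuals finish the 4-week trainings, and at 1 and 3 months follow-up after the completion". Each participant therefore has a baseline HPQ value as well as follow-up values.

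In Data analysis, the repeated-measures ANOVA is described for the effectiveness comparison on PsyCap-24, WEMWS, SWLS, CES-D and UWES. The HPQ is not in that list and has its own sentence: "Work productivity change will be compared between these two groups as well". For the ROI, "Self-reported monthly salary will be used to monetize the work productivity changes and time cost for each individual", and then "All the afore-mentioned items will be the incremental value compared with the control group".

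The only baseline score that the section names as a regressor is the CES-D, in the moderator analysis. Baseline productivity is not named as a covariate, either for the between-arm comparison or for the ROI numerator.

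**The concern.** A plain change score fixes the weight on the baseline value at 1. The weight that minimises variance is the regression slope of follow-up on baseline, which equals r when the variances are equal. For a four-week self-report of absence and performance, r may be modest. When r is below 1, subtracting the whole baseline adds noise. When r is below 0.5, it is noisier than ignoring baseline altogether.

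Two results are affected: the productivity comparison, which is a secondary outcome, and the productivity part of the ROI gain, on which the article rests its business case. The trial will yield one ROI. If that figure leans on how the arms happened to differ at baseline, it is less reliable than the collected data allow.

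**Working it through.** **Inputs from the protocol article**
- Effect size (Sample size section): "we expect to find a standard effect size of 0.3 or larger comparing the intervention group with the control group".
- Power, alpha and size (same section): "To achieve a statistical power of 80%, given a two-sided alpha of 0.05, we need at least 177 participants in each condition". The abstract gives the same arm size.
- No effect size specific to productivity and no HPQ correlation are given. The 0.3 SD effect is used here only as an illustration, and r is an assumption, shown at 0.3, 0.5 and 0.7.

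**Reproducing the plan's own figure.** n per arm = 2(1.960 + 0.842)² / 0.3² = 174.4, so 175. The t-based version gives 175.4, so 176. The stated 177 agrees. At 177 per arm the t-based power is 80.4%. The sample size is not in question.

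**Variance of the arm contrast**, in units of the outcome variance and assuming equal variances at both occasions:
- change score: 2(1 − r)
- baseline-adjusted follow-up: 1 − r²
- ratio: 2(1 − r)/(1 − r²) = 2/(1 + r)

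| r | Change | Adjusted | Ratio | Power, change | Power, adjusted | n per arm for 80%, change | n per arm for 80%, adjusted |
|---|---|---|---|---|---|---|---|
| 0.3 | 1.40 | 0.91 | 1.54 | 66.2% | 83.9% | 245 | 159 |
| 0.5 | 1.00 | 0.75 | 1.33 | 80.4% | 90.1% | 175 | 131 |
| 0.7 | 0.60 | 0.51 | 1.18 | 95.3% | 97.6% | 105 | 89 |

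Power is t-based at 177 per arm, 0.3 SD, two-sided 0.05. The n columns use the normal approximation.

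**Salary weighting.** In a simulation with an assumed log-normal salary (log-SD 0.5, 4,000 runs), the adjusted/change variance ratio for salary-valued productivity was 0.64, 0.74 and 0.83 at r = 0.3, 0.5 and 0.7. Without salary weights, (1 + r)/2 gives 0.65, 0.75 and 0.85. The mean estimate was essentially the same either way.

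**Is there bias?** In 8,000 simulated null trials per value of r, with 177 per arm, the between-arm difference in change averaged 0.000 to 0.002 SD and type I error was 5.1% to 5.3%. When only people with below-average baselines were enrolled (4,000 trials per r), the within-arm change was 0.56, 0.40 and 0.24 SD at r = 0.3, 0.5 and 0.7. The between-arm difference stayed within 0.003 SD of zero.

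**Chance imbalance.** The standard error of the baseline difference is √(2/177) = 0.106 SD. An imbalance of that size shifts the change-score estimate by (1 − r) × 0.106:
- r = 0.3: 0.074 SD
- r = 0.5: 0.053 SD
- r = 0.7: 0.032 SD

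This is the same excess variance seen from another side, because 2(1 − r) = (1 − r²) + (1 − r)². At r = 0.3 that reads 1.40 = 0.91 + 0.49. It must not be counted as a second loss.

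**The case against.** **Regression to the mean.** A reader might infer that regression to the mean distorts the productivity test or the ROI. The documents do not support that. Randomisation follows the baseline assessment, productivity is compared between arms, and every ROI item is netted against control. Regression to the mean therefore acts equally in both arms in expectation and cancels, as the simulation shows. It would distort a within-arm gain, which the netting sentence rules out.

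**Raw or unadjusted is not stated.** The article names no model for productivity. A change outcome with baseline as covariate gives exactly the same treatment estimate as ANCOVA on follow-up, so the wording does not exclude adjustment, and a fuller analysis plan may specify it. This stands for the between-arm test, where the loss is conditional on an unadjusted analysis. It carries less weight for the ROI. There the text describes arithmetic (individual changes valued at salary, totalled and netted) with no step at which baseline would be adjusted for.

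**Same contrast as the ANOVA.** For a pre/post comparison, the group-by-time interaction is itself the between-arm difference in change. So productivity is not given an odd estimator relative to the mental-health scales. This stands.

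**Borrowed magnitudes.** The 0.3 SD comes from positive-psychology evidence on well-being, and r is assumed. At r = 0.7 the power gain is about 2 points, and at r = 0.5 the change score still reaches the design power. The article states no significance test for the ROI, so the power figures apply only to the productivity comparison. All of this stands. The variance ratio does not depend on the effect size.

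**Medical cost.** Savings could equally mean a simple difference in follow-up spending between arms. The same efficiency argument reaches this item only if savings are taken as a change.

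**Conclusion.** The point holds as a matter of precision, not validity. Followed as written, Data analysis gives a change-score contrast for productivity and for the ROI productivity gain. That contrast is unbiased under randomisation and keeps its type I error. If unadjusted, it has 18% to 54% more variance than a baseline-adjusted one for r from 0.7 to 0.3, and it depends more on chance baseline imbalance in the trial as run.

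The size rests on an assumed correlation, equal variances at the two occasions, no dropout and, for power, an illustrative effect that the article does not claim for productivity. The direction does not: under equal variances the adjusted comparison is more precise at every r below 1. Nothing in the article is miscalculated or contradictory here. This is a cheap improvement to a secondary outcome and to the ROI numerator.

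**What to change.** In Data analysis:
- Compare follow-up HPQ absenteeism and presenteeism between arms with the participant's own baseline HPQ value as covariate, by ANCOVA or a baseline-adjusted mixed model.
- Take the ROI productivity gain from the between-arm difference in salary-valued follow-up productivity, adjusted for salary and salary-valued baseline productivity.
- Estimate the saving in employer-paid medical cost in the same way, with baseline past-month expenditure as covariate.

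This changes wording only. Baseline HPQ, baseline expenditure and salary are already collected, and no further participants or assessments are needed. The small downside is that the ROI is computed from a model estimate, which is a little harder to explain to employers than a sum of individual changes.

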## Discussion

### Strengths and limitations

To the best of our knowledge, this is the first experimental study that explores the applicability of PsyCap development among Asian population; and it is also one of the few studies that measure improvement in depression and mental well-being as a result of PsyCap development. We will also examine differences in these outcomes between individuals with different level of depressive symptoms. Through the investigation of changes in individuals’ work productivity from absenteeism and presenteeism, our study will be one of the few studies that quantify productivity gains and return-on-investment from any type of mental health promotion.

There are also several limitations that we need to mention. Compared with group based or individual based consultation, although web-based self-administrated interventions are usually cheaper, it might also be less effective. Meanwhile, since we will mainly use self-report method to collect data, this might cause recall bias. The ROI estimation will be less objective compared with those studies that choose one specific company and use the company records (e.g., medical claims, sick leave days) for such calculation. Another limitation would be the possible high dropout rate for this study, despite self-selection and other strategies to reduce it (e.g. email reminders and other incentives). Although studies have found that self-selected people enjoyed more obvious effects than non-self-selected individuals in PPIs [57], this also calls for caution against over-generalizing our results.

### Future implementation

If through this study, we are able to prove the intervention not only effective in improving the mental well-being of working individuals, but also bringing positive return-on-investment for employers, further efforts to improve the program, or customize it for specific industry or company is anticipated. Our research partner, the Employers’ Federation of Hong Kong would assist in this process and further funding may be sought. What’s more, a network of public and private organizations interested in the workplace mental health issues is being developed, as a side product of our recruiting efforts. We will disseminate research findings to this network and more broadly to the public. As a result, more organizations (especially those with large number of employees working under stressful condition) may be willing to invest more in similar initiatives or customize *Happy@Work* to fit their own needs in the future.

## Abbreviations

GDP: Gross domestic product; WHO: World health organization; PPIs: Positive psychology interventions; PysCap: Psychological capital; COR: Conservation of resource theory; ROI: Return-on-investment; PsyCap-24: The 24-item psychological capital questionnaire; WEMWS: Warrick-edinburgh mental well-being scale; SWLS: Satisfaction with life scale; CES-D: Centre for epidemiologic studies depression scale; UWES: The Utrecht work engagement scale - shorten version; HPQ: The WHO’s Health and Performance at Work Questionnaire; CONSORT: Consolidated standards of reporting trials; EM: Expectation-maximization.
